## Abstract

**Background:**

The purpose of this study is to compare the efficacy of prophylactic antibiotic for prevention of meningitis in acute traumatic pneumocephalus patients.

**Methods:**

In this prospective, randomized controlled clinical trial, 200 selected head injury patients with traumatic pneumocephalus are randomly assigned to receive intravenous antibiotics (2 grams Ceftriaxone twice a day), oral antibiotics (Azithromycin) or placebo for at least 7 days after trauma. The patients will be followed for one month posttrauma.

**Conclusion:**

The authors hope that this study helps clarifying the effectiveness and indications of antibiotics in prevention of meningitis in traumatic pneumocephalus after head injury and in specific subgroup of these patients.

## Background

Chemoprophylaxis with antibiotics is both feasible and desirable for prevention of a potentially serious disease when specific groups at risk can be defined and when a safe, effective, and affordable prophylactic agent is available [1]. One of such potentially serious diseases is posttraumatic meningitis. The incidence of posttraumatic meningitis after head trauma ranges from 0.2 to 17.8 per cent and increases significantly in the presence of skull base fracture, pneumocephalus or cerebrospinal fluid (CSF) leak [2,3].

Considering the serious complications of the posttraumatic meningitis, the idea of chemoprophylaxis with antibiotics for prevention of posttraumatic meningitis has always been considered rational, but the efficacy of prophylactic antibiotic agents in the setting of posttraumatic CSF leakage is still controversial. The contrasting findings reported by two large studies in which metaanalyses were conducted reflect the general disagreement and lack of sufficient power of the previous studies [4-6].

One possible reason for the inability of the previous studies to demonstrate the efficacy of prophylactic antibiotics for prevention of posttraumatic meningitis might have been inconsideration of those subsets of patients with specific risk factors [5].

With this concept in mind, the authors tried to clarify those subgroups at risk in two subsequent studies since 1994. In the first study done in our hospital ([name], [name], [name], unpublished data), the efficacy of prophylactic antibiotics in head injury patients with skull base fracture were studied. Although no statistically significant differences were found between those with and without prophylactic antibiotics, 12% of patients with skull base fractures had pneumocephalus and the incidence of meningitis was considerably higher (20%) in this subgroup of the head injury patients. In the second study we selected only patients with posttraumatic pneumocephalus. The overall meningitis rate in head injury patients with pneumocephalus was 21.5% [5]. That study again did not approve the prophylactic administration of ceftriaxone (2 grams daily) in the pneumocephalus patients. But it showed that CSF rhinorrhea and intracranial hemorrhage might be considered as primary risk factors and in the absence of them, intradural location of air and air volume greater than 10 cc as secondary risk factors for developing meningitis in posttraumatic pneumocephalus patients [5]. Even in those patients with CSF rhinorrhea or intracranial hemorrhage, prophylactic ceftriaxone (2 grams daily) did not prove to be effective on prevention of meningitis.

### Selection of drugs

In posttraumatic meningitis after traumatic pneumocephalus, the microorganisms enter the CSF from the outside mainly air sinuses. This is the reason why pneumococci are the major causative microorganisms. In order to prevent posttraumatic meningitis in pneumocephalus patients, we should either clear the air sinuses from the potential microorganisms or make the CSF defense strong enough to control those pathogenic microorganisms that have passed the blood brain barrier. This simple strategy has not worked favorably so far. There might be various reasons. We thought that the dosage of the antibiotics might have been less than enough due to lack of inflammation of the blood brain barrier. So based on the most common microorganisms in microbiological studies of the posttraumatic meningitis it has been decided to administer antibiotics with full antimeningitic dosage (2 grams Ceftriaxone twice a day) prophylactically.

Another reason for inability of the previous studies to demonstrate the efficacy of prophylactic antibiotics might have been lack of enough coverage of the normal flora of the air sinuses. These sinuses should be considered the potential source of the secondary infection in majority of cases. In order to cover these, we selected Azithromycin as an oral regimen. Penetration of drugs into the cerebrospinal fluid, minimal gastrointestinal side effects, patient tolerance and cost-effectiveness of medications were other important factors in selection of drugs.

In our previous studies meningitis happened almost always in the first week post trauma, so both regimens are continued for 7 days.

### Objectives

#### Primary objective

The primary objective of this prospective study is to compare the efficacy of prophylactic antibiotics (either intravenous Ceftriaxone 2 grams BID or oral Azithromycin) for prevention of bacterial meningitis in acute traumatic pneumocephalus.

#### Secondary objectives

- To determine the relative frequency of rhinorrhea and intracranial hemorrhage in each of the IV, O and P groups

- To determine the GCS, age and volume of intracranial air in each of the IV, O and P groups

- To determine if the volume or location of the air affects the rate of meningitis.

- To determine the rate of presence and location of the skull base fracture in each of the IV, O and P groups

- To determine the short term (during the treatment) complications of the administration of the antibiotics in each of the IV, O and P groups

- To compare the microbiological findings in meningitic patients among IV, O and P groups

- To determine the frequency of meningitis caused by resistant bacteria.

### Outcome measures

#### Primary outcome measure

The frequency of bacterial meningitis in IV, O and P groups

#### Secondary outcome measures

- The frequency of rhinorrhea, intracranial hemorrhage and skull base fracture, volume and location of intracranial air in the population study and each of the IV, O and P groups.

- The mortality rate in study population and each of the IV, O and P groups.

## Methods

### Study Population

The study is intended to be a randomized placebo-controlled clinical trial study.

### Sample size

The frequency rate of meningitis among our traumatic pneumocephalus patients was 21.5% (*p*1). What we expect to be an intended (or at least acceptable) effect of the prophylactic antibiotics is 5 %(*p*2) frequency of meningitis in the patients with antibiotics. To detect this difference with a sensitivity of 80% and an error probability of 5%, at least 62 patients per randomization group will be required using the following formula:

*n *= 7.84 * [*p*1(1 - *p*1) + *p*2 (1 - *p*2)]/[*p*_1 _- *p*_2_]^2^

Considering only comparing the placebo group with each one of the antibiotics group, our sample size should be at least 186 cases. To account for the possibility of loss to follow-up, our estimated sample size is 200 cases.

### Ethical approval

This study has been ethically approved by Sina Trauma and Surgery Research Center, Tehran University.

### Inclusion criteria

The entry criterion to this study is traumatic pneumocephalus verified by brain CT scan. The patients should be older than 15 years old, admitted less than 24 hours after trauma and we should be able to start the antibiotics in less than 24 hours after trauma.

### Exclusion criteria

Those patients who have received antibiotic therapy for other reasons within the prior 2 weeks, are on corticosteroids or allergic to the specified medications, individuals with penetrating traumatic brain injury, open skull fractures or operated for any causes, those who are discharged from hospital with personal consent, all cases with life threatening lesions including severe brain, abdominal or vascular injuries and death due to other causes will be excluded from this study.

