### Randomization

The randomization list was generated by using the website Randomization.com . The permuted block method of randomization for a block size of three was used. According to this list patients were allocated to each of the three groups in the trial: intravenous antibiotics, oral antibiotics and placebo.

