### Study design

The patients should be observed in the hospital, until occurrence of meningitis or at least 7 days after trauma. In the case of concomitant Cerebrospinal Fluid (CSF) leakage and need for close observation in the hospital, they will be hospitalized until recovery from leakage. After discharge the patients will be followed up until one month after trauma.

The following data is registered: age, sex, time interval between trauma and admission, time interval between admission and antibiotic therapy, the cause of trauma, GCS upon admission, intracranial air volume (at the time of admission and three days later), intracranial air location, presence of CSF rhinorrhea, CSF otorrhea, presence and location of the radiological signs of skull base fractures, presence and volume of the intracranial hemorrhage(at the time of admission and three days later), presence of meningitis, CSF findings, treatment and complications in the case of meningitis and one month follow-up note.

Intracranial air and hemorrhage volume are calculated in the CT scan using the formula *ABC*/2, where *A *is the greatest mass diameter by CT, *B *is the diameter 90° to *A*, and *C *is the approximate number of CT slices with mass multiplied by the slice thickness. In the case of air in the subarachnoid space, this formula is not easily applicable and an approximate volume is calculated and determined whether the volume is less than 10 cc or not [7].

The patients are divided into three groups; with intravenous antibiotics (IV), oral antibiotics (O) and placebo (P), according to the randomization list. In IV group, Ceftriaxone 2 grams BID plus oral placebo and in O group, Azithromycin 500 mg in the first day followed by 250 mg daily plus intravenous placebo for the rest will be continued for 7 days. Antibiotics should be started in less than 24 hours after trauma. Since antibiotics may mask the clinical presentation of the meningitis, these patients (IV and O) will remain hospitalized two more days for close clinical observation. In the case of meningitis, appropriate antibiotics are continued until patients' recovery. Corticosteroids should not be prescribed for the patients for any reason.

The physicians caring for the patients are not blinded to the regimen that is used.

Intracranial hemorrhages included subarachnoid hemorrhage, epidural and subdural hematoma and cerebral contusion or hematoma.

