### Statistical analysis

Intention to treat analysis will be used.

Categorical variables are compared using a chi-square test, and the Student t-test is used to compare continuous variables between groups. Logistic regression with adjustment for other possible risk factors for meningitis is used to estimate the odds ratios and 95% confidence intervals.

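### The prior-antibiotic exclusion is limited to other indications, so as worded a patient already given an antibiotic for this injury can be randomised, including to placebo

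*Protocol article*

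**What the plan says.** - **Exclusion criteria.** Prior antibiotic exposure excludes "Those patients who have received antibiotic therapy for other reasons within the prior 2 weeks". No other criterion deals with earlier antibiotics.
- **Inclusion criteria.** The patient must be "admitted less than 24 hours after trauma and we should be able to start the antibiotics in less than 24 hours after trauma". Nothing there requires the patient to have been free of antibiotics since the trauma.
- **Randomization.** With no further condition, "patients were allocated to each of the three groups in the trial: intravenous antibiotics, oral antibiotics and placebo".
- **Primary objective.** The trial is to "compare the efficacy of prophylactic antibiotics (either intravenous Ceftriaxone 2 grams BID or oral Azithromycin") in preventing bacterial meningitis.
- **Study design.** Among the registered items is the "time interval between admission and antibiotic therapy". Antibiotics given before randomisation are not listed.
- **Statistical analysis.** "Intention to treat analysis will be used", so a patient randomised to placebo is analysed as placebo whatever was given earlier.

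**The concern.** The criterion sorts earlier antibiotic exposure by its reason, and the sorting suits the trial's question badly. A patient treated for an unrelated infection ten days before is excluded. A patient given an antibiotic a few hours before because of the pneumocephalus, a CSF leak or a skull base fracture is not. The second exposure is the closer of the two to the intervention under test.

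A placebo patient who has already had prophylaxis is in part a treated patient. If that dose does anything, the placebo group's meningitis rate falls and both comparisons with placebo shrink. An earlier antibiotic could also affect CSF smear or culture, which separates confirmed from probable meningitis in the article's diagnostic definition. Through that route it reaches the secondary objectives on microbiological findings and resistant bacteria. If the exposure is not recorded, none of this can be examined afterwards.

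**Working it through.** **1. Reading the criteria together.** The exclusion reaches antibiotics given for other indications. The inclusion criteria leave up to 24 hours between trauma and study dosing and are silent on antibiotics given in that time. Randomization adds no condition. No section closes the gap, so on the plain wording the pre-treated patient is eligible for all three groups.

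**2. Reproducing the plan's sample size.** The inputs are in the Sample size section. For p1: "The frequency rate of meningitis among our traumatic pneumocephalus patients was 21.5" per cent. For p2: 5% "frequency of meningitis in the patients with antibiotics". The multiplier is 7.84 (two-sided 5%, 80% power).

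- p1(1 − p1) = 0.215 × 0.785 = 0.168775
- p2(1 − p2) = 0.05 × 0.95 = 0.0475
- n = 7.84 × 0.216275 / 0.165² = 1.695596 / 0.027225 = 62.28

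The plan states 62 per group, so its figure reproduces (63 if rounded up), and 3 × 62 = 186. The step to 200 is already assigned to loss to follow-up. The point therefore concerns wording, not arithmetic.

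**3. Upper bound on the dilution.** Assume that a share f of placebo patients was pre-treated and carries the full hoped-for effect, that is, a 5% risk. Neither the share nor the full effect comes from the article.

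- Placebo rate: q = 0.215 − f × 0.165
- Power at 62 per group: Φ( (q − 0.05) / √{[q(1 − q) + 0.0475] / 62} − 1.96 )

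With f = 0: SE = √(0.216275 / 62) = 0.0591; 0.165 / 0.0591 = 2.79; Φ(0.83) = 0.798.

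With f = 0.10: q = 0.1985; SE = √(0.206598 / 62) = 0.0577; 0.1485 / 0.0577 = 2.57; Φ(0.61) = 0.730.

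| f, full effect assumed | Placebo rate | Power, plan's unpooled variance | Power, pooled variance |
|---|---|---|---|
| 0 | 21.5% | 0.798 | 0.780 |
| 5% | 20.7% | 0.765 | 0.748 |
| 10% | 19.9% | 0.730 | 0.713 |
| 20% | 18.2% | 0.650 | 0.634 |
| 30% | 16.6% | 0.560 | 0.546 |

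**4. Less than full effect.** If the early dose carries only a fraction e of the effect, f is replaced by f × e. With 10% pre-treated and half the effect, f × e = 0.05, and power is 0.765 instead of 0.730. With no effect (e = 0), nothing is lost.

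**The case against.** **The words may mean something else.** In a trial of antibiotics, *other reasons* could be meant as reasons other than the trial regimen, which would already exclude a dose given elsewhere. The requirement that antibiotics be startable within 24 hours, and the recorded interval from admission to antibiotic therapy, fit the idea that antibiotics begin with the trial. This reading is possible, but the text does not state it, and those who screen patients apply the written criterion. If it was the intent, the rewording only makes it explicit.

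**Pre-treatment is not documented.** The article mentions neither referral from another hospital nor antibiotics before admission, and gives no frequency. This stands: the shares in the table are assumptions.

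**The full effect is not credible for an early dose.** The Background reports that ceftriaxone 2 grams daily did not prove effective in the group's previous study, even in patients with rhinorrhea or haemorrhage, and the hoped-for 5% rests on a 7-day course. The 21.5% was moreover the overall rate in a study that evaluated ceftriaxone, so it may not be a clean untreated rate. This also stands, and it confines the power figures to an upper bound.

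**A reader might infer that the placebo arm is selectively contaminated and the comparison biased.** The documents do not support that. The exposure comes before randomisation, is expected to be equally frequent in all three groups, and leaves the intention-to-treat comparison valid for the patients enrolled. What remains is dilution.

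**The two-week window has no stated starting point.** In an eligibility criterion it is naturally read as before enrolment. In a condensed article this is minor wording and not a separate defect.

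**Size and cost move together.** If many patients are pre-treated, the tighter criterion loses many; if few are, little is diluted. This is correct and is taken into account under the cost of the fix.

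**Conclusion.** The point holds as a defect in a stated criterion. As worded, an antibiotic already given for this injury does not exclude a patient, who may then be randomised to placebo, and the listed data would not show it.

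The consequence is possible dilution of both comparisons with placebo, together with a possible effect on CSF culture and the microbiology objectives. The article allows no estimate for the latter.

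The size of the dilution is unknown. If 10% of placebo patients were pre-treated and carried the full effect, power at 62 per group would fall from about 80% to about 73%. That is an upper bound for that share, and the real loss would be smaller. The rows at 20% and 30% show only how the bound moves; they should not be read as a forecast that power drops to 65% or 56%, because nothing in the article supports those shares or the full effect. The sample size calculation itself is not called into question by this point.

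**What to change.** In the Exclusion criteria, delete *for other reasons* and give the window a starting point, so that the criterion covers any systemic antibiotic, including any given for this injury, within 2 weeks before randomisation. Have this checked before allocation, so that no one is removed after randomisation.

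The cost is one reworded criterion, one screening check and the loss of some pre-treated patients from recruitment. That loss depends on the same unknown share as the dilution: to randomise 200 patients, about 200 / 0.95 = 211 otherwise eligible patients would be needed if 5% were pre-treated, and about 200 / 0.90 = 222 if 10% were. The planned sample size does not change.

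### Exclusions for self-discharge and death from other causes act after randomisation, and surgery is untimed; this contradicts the stated intention-to-treat analysis and narrows the mortality outcome

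*Protocol article*

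**What the plan says.** All places are in the protocol article.

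- **Exclusion criteria.** One sentence combines baseline conditions (recent antibiotics, corticosteroids, allergy, penetrating injury, open fracture, life-threatening lesions) with things that happen to a patient: "operated for any causes, those who are discharged from hospital with personal consent", and, at its end, "vascular injuries and death due to other causes will be excluded from this study". No time limit is attached to any of them.
- **Statistical analysis.** "Intention to treat analysis will be used". No qualification or definition follows.
- **Primary outcome measure.** "The frequency of bacterial meningitis in IV, O and P groups".
- **Secondary outcome measures.** "The mortality rate in study population and each of the IV, O and P groups", with no restriction by cause of death.
- **Study design.** "Antibiotics should be started in less than 24 hours after trauma". In-hospital observation runs until meningitis or for at least 7 days, and follow-up runs to one month after trauma. The IV and O arms stay two further days. The treating physicians know the regimen.
- **Sample size.** At least 62 per arm, 186 in all, raised to 200 to allow for loss to follow-up.

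**The concern.** Self-discharge and death from another cause are not eligibility conditions in any practical sense. A patient who has left or died is not a candidate for randomisation, so these rules bite mainly by removing patients already allocated. An analysis that removes them is not intention to treat.

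The comparison of meningitis rates, which is the primary outcome, would then be made in a set shaped by what happened after allocation. Three features of the design make it plausible that the shaping differs by arm:

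- Attribution of a death to another cause is a judgement made in open-label care.
- The diagnosis of meningitis may rest on clinical findings alone when lumbar puncture is contraindicated, so cause of death can be uncertain in the patients at risk.
- The planned hospital stay is two days longer in the antibiotic arms, so the time during which a patient can discharge himself differs by design.

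Mortality is affected directly. With other-cause deaths removed, what remains is death from meningitis, not the unrestricted rate that the outcome list names.

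**Working it through.** **1. Do the events fall after allocation?** Patients are admitted, and treatment starts, within 24 hours of trauma. The remaining in-hospital observation (at least 7 days) and the rest of the month follow allocation. The three event-type exclusions compare as follows.

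| Exclusion | When it can occur | Compatible with intention to treat? |
|---|---|---|
| Death due to other causes | Almost entirely after allocation | No |
| Self-discharge | Almost entirely after allocation | No |
| Operation for any cause | Before or after; not stated | Only if before allocation |

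No section of the article reconciles the first two rows with the intention-to-treat statement.

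**2. The plan's sample size.** Inputs from the Sample size section: p1 = 0.215, p2 = 0.05, multiplier 7.84.

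n = 7.84 × [0.215 × 0.785 + 0.05 × 0.95] / (0.165)² = 62.28

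This agrees with the stated 62, and 3 × 62 = 186. The reserve is 200 − 186 = 14 patients, and 14/200 = 7%. It is described as covering loss to follow-up only. If 7% were removed after randomisation, 200 × 0.93 = 186 would remain and nothing would be left for actual losses.

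**3. Power if patients are removed.** The shares are assumptions. Per arm, 200/3 × (1 − share) patients remain; normal approximation, two-sided 5%.

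| Share removed | Remaining per arm | Power, unpooled variance (as in the plan's formula) | Power, pooled variance |
|---|---|---|---|
| 0% | 66.7 | 82.6% | 81.0% |
| 7% | 62.0 | 79.8% | 78.0% |
| 10% | 60.0 | 78.5% | 76.7% |
| 20% | 53.3 | 73.6% | 71.6% |

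**4. Bias against the antibiotic (hypothetical).** With 66 per arm, the planned rates give 0.215 × 66 = 14.2 and 0.05 × 66 = 3.3 events, so 14 and 3 are the nearest counts. Suppose four placebo meningitis cases are removed and nobody else. Pearson chi-square without continuity correction:

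| Antibiotic events | All patients | Four placebo cases removed |
|---|---|---|
| 3/66 (4.5%) | 14/66 vs 3/66, p = 0.004 | 10/62 vs 3/66, p = 0.030 |
| 4/66 (6.1%) | 14/66 vs 4/66, p = 0.011 | 10/62 vs 4/66, p = 0.068 |

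**5. Bias in favour of one arm (hypothetical).** Let the true risk be 21.5% in both compared arms, with about 67 patients each, and let one arm alone lose a share e of patients whose risk is r. The rate among those kept is (0.215 − e·r)/(1 − e). Dividing its distance from 0.215 by the standard error of the difference and referring that to ±1.96 gives the actual type I error.

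| e | r | Rate among those kept | Type I error |
|---|---|---|---|
| 10% | 40% | (0.215 − 0.04)/0.90 = 19.4% | 5.9% |
| 10% | 60% | (0.215 − 0.06)/0.90 = 17.2% | 9.4% |
| 20% | 40% | (0.215 − 0.08)/0.80 = 16.9% | 9.9% |
| 20% | 60% | (0.215 − 0.12)/0.80 = 11.9% | 30.0% |

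Steps 4 and 5 push in opposite directions, depending on which arm loses the high-risk patients.

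**The case against.** Four points can be made on the other side.

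- **Surgery may be a baseline criterion.** The words "open skull fractures or operated for any causes" put operation next to open fracture, a baseline condition, and an operation within the first hours before entry is possible. This stands. A reader might infer that the plan removes patients for surgery after allocation; the text does not establish that. What can be said is that the timing is missing, so later surgery is caught as well.
- **The mortality outcome is not emptied.** A reader might infer that mortality cannot be estimated at all. That is too strong: only deaths from other causes are removed, so meningitis deaths remain countable. The outcome is narrowed, and it is a secondary one.
- **The result need not flip.** A reader might infer from the 4/66 row that the removals would cost the trial its significant result. At 3/66, the count nearest the planned rate, significance is kept. The scenario is also extreme: all four removed patients are placebo patients with meningitis, and no non-case is removed anywhere.
- **Selective loss of meningitis cases is not shown.** The Background says only that CSF rhinorrhea and intracranial hemorrhage might be primary risk factors. Nothing gives the number operated on, their risk, or a difference between arms.

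None of this touches the central conflict. "those who are discharged from hospital with personal consent" and death due to other causes are excluded without a time limit, and the intention-to-treat statement is unqualified. Nor is this a detail left to a fuller document: two stated rules produce two different analysis sets.

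**Conclusion.** Wrong as written. The exclusions for self-discharge and other-cause death cannot be carried out together with an intention-to-treat analysis or with the mortality rate as listed, and the surgery exclusion needs a time point. The conclusion rests on the text alone and requires no assumed rate.

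The size of the effect is unknown. The documents report no exclusion frequency and no risk among those excluded, so the figures above show only that modest, unbalanced removals can matter. The direction of any bias cannot be stated in advance. The sample-size arithmetic itself is not at fault; the reserve was simply not set aside for removals of this kind.

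**What to change.** - State that all exclusion criteria apply only up to randomisation, and that surgery excludes a patient only if it took place before allocation.
- Delete self-discharge and death due to other causes from the exclusion list.
- Analyse every randomised patient in the assigned arm, using the one-month follow-up already planned to obtain outcomes for those who leave hospital early.
- Count all deaths in the mortality outcome. Meningitis deaths can be reported separately within it.
- If the set with post-randomisation removals is of interest, keep it as a sensitivity analysis only.

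How death without meningitis enters the primary outcome can be left to the SAP.

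The cost is a change of wording, follow-up of a few more patients, and possibly a slightly diluted effect estimate. No treatment changes.
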